**Study Design and Methods**

This intervention study features a repeated measures design. Outcome measures will be assessed at McMaster University before and after a 12 week intervention. The yoga exercise intervention will be delivered at a yoga studio in downtown Hamilton, Ontario. This proof of principle study will aim to provide preliminary data supporting the use of a yoga exercise intervention in a sample of women with knee OA.

Participants

Fifty community-dwelling women, 50 years of age and older, who meet the American College of Rheumatology (ACR) criteria for clinical knee OA will be recruited to participate in this study. The ACR clinical criteria require 3 of the following:

- Knee pain on most days of the week,
- Less than 30 minutes of morning stiffness,
- Crepitus with active range of motion,
- Bony enlargement,
- Bony tenderness to palpation, and
- Signs of inflammation (warmth, swelling).

*Inclusion and Exclusion Criteria*

Women were selected because incidence of knee OA is two times greater among women than men over the age of 50 years (18-20). Muscle weakness is of particular concern in women with knee OA because their absolute muscle strength is lower compared to men, and therefore women are closer to the critical thresholds of strength required for activities of daily living (21). Finally, women report pain secondary to knee OA more frequently than men (20) perhaps because the pain experience is different (22). The incidence and prevalence of knee OA increases with age, particularly in women (18, 20, 23-25).

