The exclusion criteria for participation include a self-reported history of patellofemoral symptoms. The exercise intervention is focused on unloading the medial knee compartment; however these exercises could place large loads on the patellofemoral joint, such as squats and lunges. In addition, participants that self-report osteoporosis will be excluded. The exercise intervention includes spinal flexion and therefore may increase the risk of a fragility fracture in the spine. Exclusion criteria include diagnosis of other forms of arthritis (e.g., rheumatoid, psoriatic); active non-arthritic knee disease (e.g., gout); conditions that might be exacerbated by the protocol (e.g., unstable angina); neurological conditions such as a stroke; and current/past use of intra-articular therapies or knee surgeries and; contraindications to magnetic resonance imaging (e.g., pacemaker). Participants will be excluded if they have a skin allergy to medical tape, use an adaptive aid such as a cane or cannot climb 2 flights of stairs safely. Lower extremity trauma within 3 months, ipsilateral hip or ankle conditions, radiation (e.g., cancer treatment) and pregnancy will also be exclusion criteria. Finally, participants that have not completed an annual physical examination by a physician in the past year will be excluded. We require this exclusion criterion to minimize the potential that participants have an underlying health condition that has not been identified or managed.

*Recruitment*

Two methods of recruitment will be used. First, participants will be recruited through a list of potential participants provided by [name] at the Centre for Appendicular Magnetic Resonance Imaging (CAMRIS) at St. Joseph’s Hospital. All of the individuals on this list have signed a consent form to be contacted for research studies. These potential participants will be identified by a receptionist at CAMRIS and a letter will be sent by the receptionist on behalf of CAMRIS inviting their participation. The letter will invite participants to email or call a research assistant if interested in the study. A research assistant will respond to potential participants using the same mode of communication. Once in contact, the research assistant will describe the purpose, protocol, risks and benefits of the study. Potential participants who express an interest will be screened for the inclusion and exclusion criteria.

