Second, posters will be displayed in the Hamilton, Ontario community, including at the yoga studio. As well, the poster will be included in weekly electronic newsletters sent out by the yoga studio. The advertisement will invite potential participants to contact a research assistant via telephone or email. A research assistant will respond to potential participants using the same mode of communication. Once in contact, the research assistant will describe the purpose, protocol, risks and benefits of the study. Potential participants who express an interest will be screened for the inclusion and exclusion criteria. [name] will first meet with the potential participant at CAMRIS to confirm the presence of clinical knee OA.

For both recruitment strategies, any potential participant that expresses interest and meets the criteria for the study will be sent a copy of the consent form (electronic or hard copy at the potential participant’s discretion) and a map directing them to pre-paid parking. An appointment will be set at the MacMobilize Laboratory, McMaster University. At this time, participants will be instructed to avoid any high intensity physical activity for 24 hours prior to testing.

Yoga Intervention

The exercise intervention will be a 12-week yoga program requesting attendance at 3 supervised classes each week. Over each week, 4 classes will be available (Sunday 10-11am ; Tues, Thurs, Fri 3-4pm). Two 12-week sessions will be provided to ensure no more than 25 participants are in each session. We aim to start session one in November 2013 and session two in February 2014.

This class will be conducted at a yoga studio near downtown Hamilton in a regular temperature room (De La Sol Yoga located at the [name]; http://www.delasolyoga.com). The class will be instructed y [name]. He is a certified yoga instructor (training completed in 2008). The yoga studio is a commercial space with dedicated free parking, yoga mats and other equipment, bathroom facilities including showers, and an elevator. A structured fee is provided to the instructor and yoga studio to access space, parking and equipment. The participants will incur no costs associated with attending the yoga classes.

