Each class will be 1 hour in length. The yoga class will include a warm-up period featuring large body movements with no resistance. Then the instructor will lead the class through a series of standing postures identified with our previous work as requiring high muscle activity from the knee musculature, but minimal knee adduction moment. Examples of these postures include squats, lunges, wide-legged stances in various ranges of knee motion, and balance poses. The instructor will offer a variety of modifications for each pose, to ensure that the participants have an alternative best suited for their experience level. In addition, a series of seated poses that focus on flexibility will be completed. Each class will conclude after a guided deep-breathing and meditation activity. Throughout the class, education about knee joint anatomy, osteoarthritis and proper lower extremity alignment will be included.

Retention strategies to enhance adherence to the exercise intervention will include the following:

- Exercise logbook to track activity,
- $100 stipend upon completion of the final data collection,
- Draw for $5 Tim Horton’s gift certificate at the conclusion of some classes, and
- Rewards for best attendance across 12-weeks including a 3 month yoga pass, yoga mats, water bottles.

Outcome Measures

Outcome measures will be collected at baseline and after completion of the 12-week yoga intervention. These outcome measures will be collected at the MacMobilize Laboratory (Communications Research Laboratory Building, room B110) on McMaster campus. A study limb will be chosen as the most symptomatic knee.

*Primary Outcome Measures*

*A. Strength*

The peak torque developed during knee extension and flexion during a maximum voluntary isometric contraction will be measured by use of a Biodex System 2 isokinetic dynamometer. Data will be presented as Nm/kg. After a submaximal practice, 5 maximum-effort trials of isometric knee extension, with the knee joint positioned at 65°, will be recorded. The same protocol will be repeated for isometric knee flexion. The peak value for each of knee extension and flexion will be extracted. The reliability for these data are excellent (r=0.96) (26).

*B. Pain*

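### Knee pain is an optional entry criterion, although a fall in knee pain is a hypothesis on one of the trial's two primary outcomes

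*Protocol*

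**What the plan says.** Under Study Design and Methods, Participants, the protocol enrols women aged 50 or over "who meet the American College of Rheumatology (ACR) criteria for clinical knee OA will be recruited to participate in this study". It then defines the rule: "The ACR clinical criteria require 3 of the following". The six listed features are "Knee pain on most days of the week", short morning stiffness, crepitus, bony enlargement, bony tenderness and "Signs of inflammation (warmth, swelling". No feature is marked as mandatory.

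Three other places bear on whether an entrant has pain:

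- **Inclusion and Exclusion Criteria** lists many exclusions but no minimum pain level.
- **Recruitment** says, for women who answer posters or the newsletter, that a named person "will first meet with the potential participant at CAMRIS to confirm the presence of clinical knee OA".
- **Outcome Measures** says: "A study limb will be chosen as the most symptomatic knee".

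Primary Outcome Measures has two entries, A (strength) and B (pain), and the KOOS is the instrument under B. Each KOOS subscale runs to 100, which means no symptoms. Research Question & Hypotheses asks for a strength gain without more knee pain, and then predicts that knee pain will be reduced.

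**The concern.** The entry rule and the pain hypothesis do not fit together. The rule lets a woman qualify on, for example, short morning stiffness, crepitus and bony enlargement, with no knee pain at all. The hypothesis then expects her pain to fall.

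The KOOS has a ceiling. A woman with baseline score b on the Pain subscale can improve by at most 100 − b points, and at b = 100 by nothing. The study compares one group before and after yoga, so the average change in the enrolled women is the whole result, and no comparison group shares the same baseline mix. Women at or near the ceiling pull the average towards zero. A true benefit in painful knees could be understated or missed.

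**Working it through.** **1. The plan's one computed figure.** Sample Size Estimation uses an effect size of 0.41 for isometric knee strength, one-sided alpha 0.05 and 80% power, and states 39 participants. A one-sided paired t-test (noncentral t) gives n = 39 with power 80.8%. The normal approximation, ((1.645 + 0.842)/0.41)² = 36.8, gives 37. The stated figure is reproduced. Its effect size is for strength, so the entry rule's treatment of pain does not change it.

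**2. What the entry rule permits.** Inputs: six features, of which at least three are needed (Participants). I read the requirement as three or more.

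| Features present | All sets | Sets without pain | Sets with pain |
|---|---|---|---|
| 3 | C(6,3) = 20 | C(5,3) = 10 | C(5,2) = 10 |
| 4 | C(6,4) = 15 | C(5,4) = 5 | C(5,3) = 10 |
| 5 | C(6,5) = 6 | C(5,5) = 1 | C(5,4) = 5 |
| 6 | C(6,6) = 1 | 0 | C(5,5) = 1 |
| Total | 42 | 16 | 26 |

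So 16 of 42 qualifying sets lack the pain item. Among the minimal sets of exactly three, 10 of 20 lack it.

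**3. Does another section close the gap?**

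- The exclusions set no pain minimum.
- The confirmation visit checks for clinical knee OA, which the protocol defines only by this same rule. The visit is described only for the poster and newsletter route.
- Choosing the more symptomatic knee ranks a woman's two knees but sets no threshold. Nor is it said that the three features must be found in that knee.

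None of these makes pain a requirement.

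**4. Effect on the pain outcome.** Let f be the share of women at KOOS Pain 100 at baseline, D the mean improvement in the others, and c the mean change in those at 100, where c ≤ 0 because of the ceiling. Then

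mean improvement = (1 − f)·D + f·c ≤ (1 − f)·D.

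For D > 0 the average shrinks at least in proportion to f. The protocol gives neither f nor D, so I put no number on the loss.

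**The case against.** **Missing the item is not the same as being pain-free.** The item is pain on most days. A woman with pain on stairs, or twice a week, misses it and still has room to improve. This stands. The exact ceiling argument applies only to women at 100; others who miss the item dilute the result less, or not at all.

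**Combinations are not women.** No feature frequencies are given, and the wording about the symptomatic knee and the in-person visit suggest that a symptomatic population is intended. This also stands: 16 of 42 must not be read as 38% of the sample. But intention is not a requirement, and the text leaves entry open.

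**Strength comes first, and the primary objective is only that pain should not increase.** Largely right. Strength is outcome A and carries the sample size, and women with little pain can still worsen and so inform the no-increase question. The dilution falls on the hypothesis of reduced pain.

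**Stronger readings that the documents do not support.**

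- A reader might see a contradiction in counting "Signs of inflammation (warmth, swelling" towards entry while excluding "diagnosis of other forms of arthritis (e.g., rheumatoid, psoriatic); active non-arthritic knee disease (e.g., gout". There is none: the first is a clinical sign and the second concerns other diseases. A sign can count while women with those diseases are screened out.
- A reader might conclude that the mean pain change would drop below the 8-10 points cited for the KOOS. That needs an assumed share of pain-free women and an assumed improvement in the rest. The 8-10 range is quoted as a property of the scale; Statistical Analyses tests only p<0.05.

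**Conclusion.** The point holds in a limited form. As written, the rule lets women with little or no knee pain into a study that predicts a fall in knee pain and measures it on a scale with a ceiling. This follows from the protocol's own text and needs no outside definition of knee OA; whether the list matches the published criteria cannot be checked here and is not part of the point.

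The size is 16 of 42 qualifying feature sets without the pain item. That measures how open the rule is, not how many women enter through the gap; the affected share is unknown. The conclusion assumes that three means at least three, and that the KOOS Pain subscale is the pain measure intended under Primary Outcome Measures, B. The strength outcome and the figure of 39 are not affected.

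**What to change.** Reconcile the entry rule with the pain outcome. In Participants, make "Knee pain on most days of the week" a required item, assessed in the study knee, and keep the present total of three features: pain plus at least two of the other five. Of the 42 sets, 26 remain and none lacks pain.

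A stricter rule is not needed to close this gap. Requiring pain plus at least three of stiffness, crepitus, enlargement and tenderness, with inflammation no longer counted, would keep only (C(4,3) + C(4,4)) × 2 = 10 of the 42 sets, the factor 2 covering inflammation present or absent. It would also turn away many women who do have pain, and nothing in the protocol supports it.

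The cost is one sentence of eligibility wording before recruitment and a smaller eligible pool. How much smaller cannot be said without feature frequencies. Once women are enrolled, the mismatch can only be described, for instance by reporting the baseline distribution of KOOS Pain and the number of women at 100.

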- The Six-Minute Walk Test (6MW) is used to quantify walking ability. The 6MW is an inexpensive clinical tool that involves recording the distance that participants cover while walking indoors at their own pace for 6 minutes. Participants are free to stop or use a mobility aid to complete the walking task, making this measure clinically useful. The 6MW measurement will be recorded indoors in a well-lit, tiled rectangular hallway. The score recorded is the total distance traveled in 6 minutes. Instructions for the 6MW will correspond with the published protocol (44). The 6MW yields highly reliable (intraclass correlation coefficient=.96) and valid data (45).
- Participants will be asked to ascend and descend a 9-step staircase as quickly as possible, without compromising their safety. The hand rail can be used as needed. The participants will be asked to start at the base of the stairs at a distance from the first step of their choosing. The participants will be instructed not to run or jog, and not to skip any steps. Time to ascend and descend will be recorded separately, to the nearest 10^th^ of a second, using a stopwatch. Participants will be asked to repeat this procedure two times, where scores from only the ascent and descent on the second attempt are recorded. Data from our laboratory demonstrate excellent test-retest reliability of the stair ascent and descent tasks among 29 adults (ICC=0.881, 0.843 respectively).
- The 30 second chair stand task quantifies the number of sit-to-stand movements that can be completed within 30 seconds, starting from a seated position in an armless chair of a standard height (45 cm). After an opportunity to practice the task, participants will be asked to perform this task at a comfortable pace. Knee extensor strength has been shown to be a strong predictor of performance on repeated chair stand tests (46). In addition, lower extremity muscle power was predicted from performance of the 30 second chair stand in 14 older adults (47).

*C. Cardiovascular Measures of Fitness*

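### Stair ascent: each woman picks her own starting distance, and nothing fixes, records or repeats it at follow-up or says what starts the watch

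*Protocol*

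**What the plan says.** The stair test is described in the Protocol under Secondary Outcome Measures, B. Mobility Performance Measures. The task is a fast one: "Participants will be asked to ascend and descend a 9-step staircase as quickly as possible, without compromising their safety". The start position is left open: "The participants will be asked to start at the base of the stairs at a distance from the first step of their choosing". Timing is specified only as: "Time to ascend and descend will be recorded separately, to the nearest 10^th^ of a second, using a stopwatch". Two rules restrain the performance. One concerns gait: "The participants will be instructed not to run or jog, and not to skip any steps". The other concerns scoring, with two attempts made and the second counted: "where scores from only the ascent and descent on the second attempt are recorded".

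The same paragraph reports the laboratory's own test-retest ICCs in 29 adults, 0.881 for ascent and 0.843 for descent. It does not say whether those adults chose their own start or how far apart the two tests were.

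On the comparison itself, the Outcome Measures section says: "Outcome measures will be collected at baseline and after completion of the 12-week yoga intervention". The design is stated as: "This intervention study features a repeated measures design". No control group is described. Statistical Analyses plans a repeated measures analysis of variance for all primary and secondary outcomes.

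**The concern.** The start rule is a positive instruction, so it is not a gap that an analysis plan could later fill. A distance that was never standardised or written down cannot be recovered at analysis.

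A woman may stand in one place at baseline and in another 12 weeks later. Depending on when the watch starts, the difference enters her ascent time either as extra or saved approach time, or as a different speed on reaching the first step. If such differences point in no common direction, they widen the spread of the change scores and cost precision. If they lean one way on average, for example because women are more familiar with the task at follow-up, the mean change moves. With no comparison group, that movement would be read as part of the effect of yoga. Improved mobility performance is a named secondary objective, and the stair test is one of three measures of it.

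**Working it through.** **Does any other text close the gap?** The Protocol's lists of baseline and follow-up measures name the mobility tests only as a group. Nothing there, or elsewhere, marks a start line, records the distance, ties follow-up to baseline, or defines when timing begins. The no-running rule limits gait, and scoring the second attempt gives practice within a visit. Neither fixes the distance between visits.

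**Size for one woman, if timing starts when she leaves her spot.** The shift is the change in distance divided by walking speed. Both inputs are assumptions, because the Protocol gives neither.

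| Change in distance | at 1.3 m/s | at 0.8 m/s |
|---|---|---|
| 0.25 m | 0.25 / 1.3 = 0.19 s | 0.25 / 0.8 = 0.31 s |
| 0.50 m | 0.50 / 1.3 = 0.38 s | 0.50 / 0.8 = 0.63 s |

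The range is about 0.2 to 0.6 s, against a recording unit of 0.1 s. I give no percentage of the ascent time, because the Protocol states no typical stair time.

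**Size if timing starts at first-step contact.** Approach time contributes nothing. Only the speed at which she meets the first step can differ, and running and jogging are barred. The effect is smaller, and the Protocol gives nothing from which to compute it.

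**What the reported ICC implies for the mean.** Let SD be the between-person standard deviation of ascent time, and assume that the ICC of 0.881 carries over to these women.

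- Standard error of measurement: SD × √(1 − 0.881) = 0.34 SD.
- SD of the change between visits: SD × √(2 × 0.119) = 0.49 SD.
- With 39 completers (the number in Sample Size Estimation), the mean change that reaches two-sided p<0.05 is 2.024 × 0.488 SD / √39 = 0.16 SD.

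So a small average drift would be enough. As an illustration, suppose there is no true change but the average ascent time shifts by 0.25 s. A paired t-test on 39 women would call this significant with probability about 0.88, 0.55 or 0.35 for an assumed SD of 1.0, 1.5 or 2.0 s. At 0.8 to 1.3 m/s, an average shift of 0.25 s needs an average change in distance of 0.25 × 0.8 = 0.20 m to 0.25 × 1.3 = 0.33 m, all in one direction. This again holds only if the approach is timed. Nothing in the Protocol shows that such a drift would occur.

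**The Protocol's own sample size.** The stated 39 reproduces: a one-sided paired t-test at 0.05 with effect size 0.41 has power 0.81. It rests on knee strength, not on stair time, and this point does not change it.

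**The case against.** The best reply is the laboratory's reliability data. ICCs of 0.881 and 0.843 are the only evidence in the Protocol on noise in stair times. If they came from the same free-start procedure, variation in starting distance is already inside them, and random noise is modest. That much stands. It is incomplete, because the Protocol does not say that the procedure was the same, and because an ICC does not exclude a systematic shift over 12 weeks.

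Second, women start at the base of the stairs, which limits how far the distance can plausibly vary. This also stands, and is why the working stops at 0.5 m.

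Third, a reader might infer that the whole stair test is compromised. The text does not support this. The free choice concerns the base of the stairs, and the descent is timed separately.

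Fourth, a reader might infer that the rule produces a false mobility gain comparable to a training effect. The text does not support that either. The Protocol gives no expected stair improvement to compare with, the 0.2 to 0.6 s is one woman's shift and not a group mean, and changes that are as often closer as farther add noise without bias.

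Finally, this is one part of one secondary outcome in a study that describes itself as proof of principle. That is correct and sets the severity.

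**Conclusion.** The point holds for the stair ascent, at minor severity. The Protocol lets a quantity chosen by the participant enter a before-after outcome without fixing, recording or repeating it, and leaves the start of timing undefined. The certain consequence is an avoidable source of variation. The possible one is a drift that could not be separated from the effect of the intervention. The figure of 0.2 to 0.6 s per woman depends on assumed changes in distance (0.25 to 0.5 m), on assumed speeds (0.8 to 1.3 m/s), and on timing that starts when she leaves her spot. Under first-step timing the effect is smaller. Bias in the mean is possible but not shown. The primary outcomes, strength and pain, are unaffected.

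**What to change.** Replace the self-chosen distance with one floor mark, used by every woman at both visits. If free choice is to be kept for comfort, measure the distance each woman chooses at baseline and have her start from the same distance at follow-up. In either case, state the event that starts the stopwatch and use it at every test. The cost is a strip of tape and a sentence or two in the Protocol, but it has to be in place before baseline testing. The one small downside is that times would be slightly less comparable with the laboratory's earlier reliability data, if those used a free start. It would help to say whether they did.

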Yoga is an exercise activity that emphasizes controlled, fluid movements through a variety of static postures. Many yoga postures challenge and strengthen musculature of the lower extremity, while minimizing some potential negative effects that other exercise programs pose for people with knee OA. For example, running is an activity that includes large and repetitive loads on the knee, which may not be the best-suited activity for individuals with knee OA. Yoga has beneficial effects on various aspects of quality of life, including improved cardiorespiratory health, body awareness, well-being and mental health. Further, yoga has been shown to improved strength, balance, flexibility, pain, and disability in older adults and individuals with knee OA (12) (13) (14) (15) (16) (17). For example, a pilot study consisting of 7 women over age 50 years with symptomatic knee OA implemented an 8-week program of modified yoga postures. Each week participants attended one 90-minute weekly class. Participants reported improvements in knee pain, physical function and mental health, demonstrating that yoga holds great potential as a treatment option for older, yoga-naive women with knee OA (16).

We recently completed a biomechanical analysis of ten common yoga postures that emphasize lower extremity strengthening, including squats, lunges and balancing postures in 30 young women [not yet published]. These analyses focused on the knee adduction moment and muscle activation patterns to identify postures that did not overload the medial knee while requiring enough muscle activity to result in strengthening. Of the ten yoga postures, eight produced negligible knee adduction moments and all required muscle activations that would facilitate strengthening of the quadriceps and hamstrings [not yet published]. These data provide the foundation for an intervention that emphasizes the eight yoga postures that result in negligible knee adduction moments.

Research Question & Hypotheses

The primary objective of this study is to determine whether a yoga exercise intervention will improve the strength of the musculature that surrounds the knee without increasing knee pain in women with knee osteoarthritis (OA). A secondary objective is to determine whether a yoga exercise intervention will reduce the knee adduction moment during gait, improve mobility performance, and improve cardiovascular fitness.

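### The 30-second chair stand is defined as the number of stands that can be completed but is run at a comfortable pace, so the count mixes chosen pace with ability

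*Protocol*

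**What the plan says.** The chair stand is the third test under Secondary Outcome Measures, B. Mobility Performance Measures, in the Protocol's Study Design and Methods.

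- **Definition of the score:** the task "quantifies the number of sit-to-stand movements that can be completed within 30 seconds".
- **Instruction:** after a chance to practise, "participants will be asked to perform this task at a comfortable pace".
- **Rationale:** "Knee extensor strength has been shown to be a strong predictor of performance on repeated chair stand tests", and "lower extremity muscle power was predicted from performance of the 30 second chair stand in 14 older adults".

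The other two tests in the subsection state their pace in their own descriptions. The stair test asks participants to "ascend and descend a 9-step staircase as quickly as possible, without compromising their safety". The six-minute walk records the distance covered while "walking indoors at their own pace for 6 minutes" and follows a cited published protocol.

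The three tests serve the secondary objective, which is to "reduce the knee adduction moment during gait, improve mobility performance, and improve cardiovascular fitness". On design, the Protocol states: "This intervention study features a repeated measures design". Measurements are taken before and after 12 weeks of yoga, and no control group is described. The procedure list near the end of the Protocol names the mobility measures only as a group, and nothing elsewhere explains the comfortable pace.

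**The concern.** The definition and the instruction stand next to each other and describe different quantities. The number of stands a woman can complete in 30 seconds is a maximum. The number she completes at a pace she finds comfortable depends on what she is able to do and also on how fast she chooses to go. Strength and power, which the paragraph uses to justify the test, belong with the first quantity.

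What is at stake is how the pre-to-post change is read. The Statistical Analyses section attributes changes in the outcomes to the yoga intervention. With no control group described, nothing in the design separates a change in preferred pace from a change in ability. Preferred pace could move either way:

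- **Upward:** participants know the task at the second visit, may expect to have improved, and have practised squats in class.
- **Downward or flat:** the Introduction characterises yoga by movement under control. A woman trained in that style may choose a more deliberate rise even though she has become stronger.

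The first would look like a benefit that is not there. The second would hide one that is.

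**Working it through.** **1. Is there a figure in the plan to reproduce?** Not for this outcome. The Protocol gives no mean, standard deviation, reliability or meaningful change for the chair stand. It does give reliability for the walk (0.96) and for stair ascent and descent (0.881 and 0.843).

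The only computed figure in the document is the sample size of 39, from an effect size of 0.41 for isometric knee strength, one-sided alpha 0.05 and 80% power. A paired t-test with the noncentral t distribution gives power 0.798 at n = 38 and 0.808 at n = 39, so 39 reproduces. It does not use the chair stand and is not affected by this point.

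**2. The text side by side.**

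| Test | What is scored | Pace instruction | Do they agree? |
|---|---|---|---|
| Six-minute walk | Distance covered in 6 minutes | Own pace, stated in the description | Yes |
| Stairs | Time up and time down | Fastest safe speed | Yes |
| Chair stand | Stands that can be completed in 30 seconds | Comfortable pace | No |

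Only the chair stand has a definition and a pace instruction that disagree. It is also the only one of the three with neither a cited procedure nor a reliability figure.

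**3. How far could pace alone move the count?** All inputs here except the 30 seconds are assumptions: 2.0, 2.5 or 3.0 seconds per stand, and a shift of 10% in time per stand.

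Count = 30 / t, where t is seconds per stand. With 10% less time per stand, the count is 30 / (0.9 t), a ratio of 1 / 0.9 = 1.111, or +11% at any starting pace.

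| t (s) | 30 / t | 30 / (0.9 t) | Change |
|---|---|---|---|
| 2.0 | 15.0 | 30 / 1.80 = 16.7 | +1.7 |
| 2.5 | 12.0 | 30 / 2.25 = 13.3 | +1.3 |
| 3.0 | 10.0 | 30 / 2.70 = 11.1 | +1.1 |

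For the opposite shift, 10% more time per stand gives a ratio of 1 / 1.1 = 0.909, or -9%. The counts become 30 / 2.20 = 13.6 (-1.4), 30 / 2.75 = 10.9 (-1.1) and 30 / 3.30 = 9.1 (-0.9).

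This shows how sensitive the count is to pace. It does not show that a shift of this size will occur.

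**The case against.** The strongest reply is that the Protocol promises mobility performance, not capacity, and that the number of stands a woman with knee osteoarthritis manages comfortably is a reasonable measure of performance. The six-minute walk is also self-paced, so the subsection has no uniform maximal-effort rule for the chair stand to break. Motivation, expectation and familiarity would affect a maximal test too, and the practice opportunity already deals with part of the familiarity. Strength is measured directly by dynamometer, so the chair stand is not needed as a proxy for it. The 10% shift is assumed.

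Much of this stands, and it rules out several stronger readings that a reader might infer:

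- **That the test measures pace rather than ability.** Nothing in the Protocol shows this. A comfortable-pace count probably still partly reflects function.
- **That the cited strength and power evidence does not apply.** This would require knowing the pace used in the cited studies, which the Protocol does not report. What can be said is that the Protocol does not show that the evidence carries over.
- **That the stair test sets the standard for the whole subsection.** The walk test is self-paced, so it does not.
- **That a maximal instruction would remove motivation and expectation effects.** It would not, because those come from the before-after design.

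What the reply does not answer is the disagreement within the chair-stand paragraph itself. The walk is self-paced and says so in its definition. The chair stand is defined as a maximum, justified by strength and power, and then run at a comfortable pace with no reason given. Nor does a wish to limit exertion explain it, since the Protocol already asks for maximum-effort isometric contractions and the fastest safe stair climb.

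**Conclusion.** The point holds as an inconsistency between the stated score and the instruction for one secondary measure. Followed as written, the test yields a count in which chosen pace and ability are mixed, and a before-after change in it cannot be assigned cleanly to either.

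The possible size, under the assumed 10% shift and 2.0 to 3.0 seconds per stand, is about 1.1 to 1.7 stands upward or 0.9 to 1.4 downward. The Protocol has no figure against which to judge whether such a shift is likely or important, so this range is illustrative only.

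The consequence is limited. Knee strength and KOOS pain, the primary outcomes, do not depend on this test. It is still worth correcting, because the measure serves a stated secondary objective and cannot be repaired once baseline counts have been taken under a different instruction.

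**What to change.** Reconcile the two sentences before the first baseline visit. The simplest way is to make the instruction match the definition already given: as many full stands as possible in 30 seconds without compromising safety, read from the same script at baseline and follow-up. The safety condition is the one the stair test already carries.

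The change is one line of test instruction, with no added visit, equipment or analysis. The cost to participants is slightly more effort in a task already limited to 30 seconds.
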